### Sample size calculation

The primary outcome of this trial is the 6MWT distance (meters). The sample size was calculated for a two-arm parallel randomized controlled trial using the standard formula for comparing two independent means [88]. Assumptions included a two-sided α = 0.05, statistical power (1 − β) = 0.80, a clinically relevant between-group difference (Δ) of 60 m, based on perioperative colorectal cancer studies reporting minimal clinically important differences of approximately 60–75 m in the 6MWT [7], and a standard deviation (σ) of 80 m, consistent with previous randomized prehabilitation trials in similar populations [5,89]. Under these parameters, the estimated requirement was 23 participants per group (n = 46 in total). To account for an anticipated dropout rate of approximately 20%, the final target sample size was increased to 28 participants per group, resulting in a total of 56 participants. This sample size is expected to provide adequate statistical power to detect clinically meaningful differences in functional capacity while mitigating the impact of potential attrition [90].

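### The stated sample-size inputs require 28 evaluable participants per group (29 with the t distribution), not 23, so the printed calculation does not support 80% power

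*Protocol article*

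**What the plan says.** All inputs and the result stand together in the protocol article, Methods, Sample size calculation. The method is described as "using the standard formula for comparing two independent means". The inputs are:

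- level: "Assumptions included a two-sided α = 0.05"
- power: "statistical power (1 − β) = 0.80"
- difference: "a clinically relevant between-group difference (Δ) of 60 m"
- variability: "a standard deviation (σ) of 80 m"

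The result is: "Under these parameters, the estimated requirement was 23 participants per group (n = 46 in total". The next step reads: "To account for an anticipated dropout rate of approximately 20%, the final target sample size was increased to 28 participants per group", which makes 56 in total. The section ends with the assurance: "This sample size is expected to provide adequate statistical power to detect clinically meaningful differences in functional capacity".

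Allocation is 1:1 (Allocation and blinding). The calculation mentions no baseline correlation, repeated measures, one-sided test or other device that would lower the requirement. The Statistical analysis section uses a two-sided 5% threshold throughout. It plans linear mixed models adjusted for age and sex, and ANCOVA adjusted for the T1 value at each later visit.

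**The concern.** This calculation is the article's only justification for the size of the trial on its primary outcome. The formula it names has a closed form and every input is printed, so the result can be checked directly. It does not come out. The gap is five or six participants per group, about 18–21% of the requirement, which is more than rounding or the choice between normal and t distributions can explain.

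What is at stake is how the primary result is read. If the 80% figure stands, a non-significant result may be given more weight as evidence against a 60 m benefit than the calculation warrants. The article cites a range of roughly 60–75 m for the minimal clinically important difference, and 60 m is its lower end. The shortfall therefore falls at the value that the investigators chose to target.

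**Working it through.** **Inputs**, all from the Sample size calculation section: two-sided α = 0.05 (z = 1.960), power 0.80 (z = 0.842), Δ = 60 m, σ = 80 m, standardised difference 60/80 = 0.75. Allocation is 1:1.

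**1. Attempt to reproduce 23 per group.** The formula for two independent means is

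n per group = 2 (z₁₋α/₂ + z₁₋β)² σ² / Δ² = 2 × (1.960 + 0.842)² × 80² / 60² = 27.9, so **28**.

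With the noncentral t distribution the solution is 28.9, so **29**. The stated 23 is not reproduced either way.

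**2. What would give 23.** Each of these routes contradicts the text or adds something it does not say:

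- one-sided 5%: 22 (normal) or 23 (t)
- 70% power, two-sided: 22 (normal) or 23 (t)
- a difference of about 67 m (normal) or 68 m (t)
- an SD of about 72 m (normal) or 70–71 m (t)
- ANCOVA with a baseline correlation of about 0.42–0.45
- a change score with a correlation of 0.6

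**3. Dropout step.** 28 × (1 − 0.20) = 22.4 per group remain. Inflating 23 correctly gives 23 / 0.80 = 28.75, so 29; the printed 28 matches 23 × 1.2 = 27.6. Inflating the correct requirement gives 28 / 0.80 = 35 (normal) or 29 / 0.80 = 36.25, so 37 (t), per group.

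**4. Power for 60 m, and the difference detectable with 80% power** (unadjusted comparison, SD 80 m, two-sided 5%). The normal form for the detectable difference is (1.960 + 0.842) × 80 × √(2/n).

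| Evaluable per group | Power, t | Power, normal | Detectable, t | Detectable, normal |
|---|---|---|---|---|
| 22.4 (28 less 20%) | 68.9% | 70.9% | 68.5 m | 67.0 m |
| 23 (as stated) | 70.1% | 72.0% | 67.6 m | 66.1 m |
| 28 (no dropout) | 78.7% | 80.1% | 61.0 m | 59.9 m |
| 29 | 80.1% | 81.5% | 59.9 m | 58.9 m |

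The third row shows that 28 per group comes to about 80% only if nobody is lost.

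**5. Effect of baseline adjustment.** The article gives no correlation between T1 and later walk distance, so the values below are assumptions. The residual SD is taken as 80 × √(1 − ρ²), with 22 evaluable per group and the t distribution:

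| Assumed ρ | Residual SD | Power for 60 m |
|---|---|---|
| 0.3 | 76.3 m | 72% |
| 0.4 | 73.3 m | 76% |
| 0.5 | 69.3 m | 80% |
| 0.6 | 64.0 m | 86% |
| 0.7 | 57.1 m | 93% |

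**The case against.** The strongest reply is that the trial will not be analysed with the test used for sizing. The Statistical analysis section plans a mixed model with T1 among its visits, and ANCOVA adjusted for T1. If walk distance at T1 correlates at 0.5 or more with the later value, 22 per group reach 80% for 60 m. This stands. A reader might infer that the trial simply has 69% power and a type II error of 31%. The document does not support so flat a statement, because those figures belong to an unadjusted t-test in 22.4 completers per group. The reply does not rescue the printed calculation, though. That calculation names two independent means and uses no correlation, and an unstated assumption cannot carry a stated 80%.

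It may also be said that multiple imputation keeps all 56 in the analysis. Under missing at random it keeps them in the dataset but does not restore the information in unobserved outcomes. The section itself inflates for dropout.

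The dropout step is only a side remark. The text says approximately 20%, 28 per group still leave 23 at a loss of 5/28 = 17.9%, and the difference from the correct inflation is one participant per group.

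A reader might also infer that a one-sided test was used. The text does not show this. The normal formula gives 22 one-sided, only the t version gives 23, and several other routes arrive at the same number. The source of 23 cannot be identified from the article.

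Finally, the Discussion already lists the relatively small sample as a limitation. That is fair context, but it does not correct the figure.

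**Conclusion.** The point holds. On the article's own inputs the requirement is 28 evaluable per group (29 by t), that is 56–58 in total, against the stated 23 and 46. The claim of 80% power does not follow from the calculation given for it. For the unadjusted comparison that it names, power for 60 m is about 70–72% at 23 per group and about 69–71% at the 22.4 expected after 20% loss. The detectable difference at 80% power is about 66–69 m across these cases. On these inputs the target of 56 holds no real attrition allowance.

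These figures rest on an SD of 80 m, equal groups and no baseline adjustment. The power of the planned adjusted analysis may be higher, and may reach or exceed 80%, but the article gives nothing from which to say by how much.

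**What to change.** Keep 56 participants and correct the Sample size calculation section before results are known; the Data management section defers analysis until all assessments are final, so there is room to do so. Delete the 23 per group and 46 in total, then choose one of two statements:

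- **(a)** State that 56 randomised with about 20% dropout give about 69–71% power for 60 m, or 80% power for about 67–69 m, for an unadjusted two-group comparison.
- **(b)** Redo the calculation for the baseline-adjusted comparison at a named visit, with an explicitly assumed and justified T1 correlation, and show power over a range such as the one tabulated above. Because the sample size is already fixed and recruitment is under way, the correlation should be justified from outside this trial's data and labelled as an assumption.

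In either case use n/(1 − dropout) for the attrition step.

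The change is to wording only and needs no extra patients. The price is a stated power that is less favourable under (a) or openly conditional under (b).

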### Data management

A secure and structured database will be developed to systematically track each participant’s progress during the study, including all clinical assessments and outcome measures. Data will be recorded in real time and stored on password-protected, encrypted computers, with access strictly limited to authorized members of the research team directly involved in the study.

All participants will be assigned a unique identification code to ensure the confidentiality and anonymization of personal information. An independent researcher will oversee the data collection process to ensure protocol adherence, monitor data quality and completeness, and safeguard participant safety throughout the study.

Data analysis will be performed only after participant recruitment is complete and all outcome assessments have been finalized.

### Statistical analysis

All statistical analyses will be performed using the Statistical Package for the Social Sciences (SPSS), version 30.0 (IBM Corp., Armonk, NY, USA). A two-sided p-value < 0.05 will be considered statistically significant for all tests.

Descriptive statistics will be used to summarize the baseline characteristics and outcome variables. Categorical variables will be reported as frequencies and percentages, whereas continuous variables will be expressed as means and standard deviations (or medians and interquartile ranges, as appropriate), together with 95% confidence intervals. The Shapiro–Wilk test will be used to assess the normality of continuous variables. To verify baseline comparability between the two groups, parametric or non-parametric tests will be selected based on data distribution: t-tests or Mann–Whitney U for continuous variables, and Chi-square tests for categorical variables.

To evaluate the effect of the intervention over time, linear mixed-effects models will be applied to account for within-subject correlations in longitudinal data. The primary models will include participant-level random intercepts, with time modeled as a categorical fixed effect, together with group and the group-by-time interaction. The covariance structure will be selected on the basis of model fit and parsimony. Random slopes for time will be explored in sensitivity analyses if supported by model fit and data structure. Prespecified adjustment variables beyond the main fixed effects will include the stratification factors used in randomization, namely age and sex. When significant interaction effects are observed, Bonferroni-adjusted post hoc tests will be used to identify pairwise differences.

Between-group comparisons at each time point will be conducted using analysis of covariance (ANCOVA), adjusting for baseline values (T1). Differences in categorical outcomes will be analyzed using the Chi-square test or Fisher’s exact test, as appropriate.

All analyses will be conducted under the intention-to-treat (ITT) principle, including all randomized participants in the groups to which they were originally assigned, regardless of adherence or protocol deviations. Missing data will be handled using multiple imputation under a missing-at-random assumption, with the imputation model incorporating treatment group, time, baseline measures, and other variables associated with missingness, as appropriate.

Effect sizes will be calculated to quantify the magnitude of differences observed, using Cohen’s d for parametric comparisons and effect size r for non-parametric comparisons, both for within- and between-group analyses of the main outcomes.

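### The primary mixed model for 6MWT omits baseline as a covariate and gates its pairwise tests behind the interaction, and the plan does not say which test or visit decides the trial

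*Protocol article*

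**What the plan says.** All of this is in the Protocol article.

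- **Primary model (Statistical analysis).** A linear mixed model with a participant random intercept, categorical time, group and group-by-time. On covariates: "Prespecified adjustment variables beyond the main fixed effects will include the stratification factors used in randomization, namely age and sex". Baseline 6MWT is not listed.
- **Visit-level tests within that model.** "When significant interaction effects are observed, Bonferroni-adjusted post hoc tests will be used to identify pairwise differences". The pairs are not defined.
- **Second analysis (next paragraph).** ANCOVA comparing the groups at each time point, adjusted for T1. No interaction gate or multiplicity level is attached, and it is not described as primary, supportive or sensitivity.
- **Visits.** The Procedure section makes T1 to T4 in-person and T5 a telephone interview. The Discussion confirms four 6MWT assessments.
- **Sample size calculation.** Made "using the standard formula for comparing two independent means", with "a clinically relevant between-group difference (Δ) of 60 m" and "a standard deviation (σ) of 80 m". No visit, interaction, repeated measure or multiplicity adjustment enters it.

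**The concern.** Baseline 6MWT is collected on everyone and should be a strong predictor of later 6MWT. The model labelled primary does not list it as a covariate. If T1 is one of the time levels, that model's visit contrasts are either raw group differences at a visit or differences in change from T1. Both are less precise than a baseline-adjusted difference. They are also reached only through a 3-df interaction test, and then at a reduced significance level.

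The ANCOVA has neither drawback, but nothing says it decides the trial. Two analyses of the same outcome with quite different power can disagree, and the text gives no rule for which one is believed. The sample size was worked out for a single contrast and does not describe the gated route.

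**Working it through.** **Inputs from the article.** "Assumptions included a two-sided α = 0.05, statistical power (1 − β) = 0.80"; difference 60 m; SD 80 m; "the estimated requirement was 23 participants per group (n = 46 in total"; 28 per group randomized with about 20% dropout. Retaining 80% leaves 28 × 0.8 = 22.4, so 22 to 23 evaluable per group.

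**Assumptions, not in the article.** T4 is the decisive visit. The correlation ρ between any two visits is equal, from 0.5 to 0.8. True group differences at T1–T4 are 0/0/0/60, 0/20/40/60 or 0/60/60/60 m. Age and sex effects are not modelled.

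**1. The plan's own figure.** n = 2(1.960 + 0.842)² × 80² / 60² = 27.9, so 28 per group. The stated 23 is not reproduced; a one-sided α gives 22.0 (23 with the t distribution). An unadjusted two-sided t comparison with 23 per group has 70% power. This is a separate point, but it means there is no spare power to give away.

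**2. Relative precision at one visit.** Variances of the per-person quantity compared:
- raw value at T4: σ²
- change from T1: 2σ²(1 − ρ)
- baseline-adjusted: σ²(1 − ρ²)

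Change relative to baseline-adjusted is 2/(1 + ρ): 1.33 at ρ = 0.5, 1.18 at 0.7, 1.11 at 0.8. Raw relative to baseline-adjusted is 1/(1 − ρ²): 1.33, 1.96 and 2.78.

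**3. The interaction test alone.** With four visits and two groups it has 3 df. The noncentrality is λ = (n/2) Σ(d − d̄)² / [σ²(1 − ρ)]. For 23 per group, ρ = 0.5 and 0/20/40/60, Σ(d − d̄)² = 2000 and λ = 11.5 × 2000 / 3200 = 7.19, giving 59% power. For 0/0/0/60 the sum is 2700 and λ = 9.70, giving 73%.

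**4. One ungated baseline-adjusted T4 contrast.** The residual SD is 80√(1 − ρ²), which is 69.3 m at ρ = 0.5. With 23 per group, 60 / (69.3 × √(2/23)) = 2.94, and the noncentral t gives 82% (80% with 22). The formula ignores the small cost of estimating the baseline slope; allowing for it gives about 79–81%.

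**5. The gated routes.** Simulated with 20,000 runs per cell: interaction p < 0.05, then T4 at the Bonferroni level. Power with 23 per group, as the range over the three patterns:

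| Route | ρ = 0.5 | 0.6 | 0.7 | 0.8 |
|---|---|---|---|---|
| Interaction alone | 59–73% | 70–83% | 82–93% | 95–99% |
| Gate, raw T4 difference at 0.05/4 | 37–44% | 40–47% | 44–48% | 48–49% |
| Gate, T1-to-T4 change at 0.05/3 | 50–53% | 62–65% | 77–80% | 93–94% |
| Ungated baseline-adjusted T4 (formula) | 82% | 87% | 94% | 98% |

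With 22 per group the gated rows fall slightly: at ρ = 0.5, 35–41% for the raw difference and 49–50% for change. Re-running with the T4 variance estimated from that visit alone lowers the raw row by a further one or two points (33% in the lowest cell). Dividing by 3 instead of 4 raises the raw row to 39–53% with 23 per group.

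**The case against.** The best defence is that the plan already contains the efficient analysis. The ANCOVA at each visit adjusts for T1 and is not gated, and its T4 comparison has about 79% power or more over the whole correlation range. Three stronger readings are therefore tempting, and the text does not support them.

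- *Visit differences are examined only after a significant interaction.* True within the mixed model, but not of the plan as a whole, because of the ANCOVA.
- *The primary model ignores baseline.* If T1 is a time level, which is the natural reading but is not stated, the interaction compares changes from baseline. Baseline is then used, though less efficiently.
- *Power is far below 80%.* Not in general. At a correlation of 0.7 or more the interaction test alone exceeds 80% in all three patterns, and at 0.8 so does the gated change contrast. The article gives no correlation, names no decisive visit and does not define the post hoc pairs.

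A reader might also infer that the ANCOVA leaves out age and sex. Its sentence does not say, and a condensed article may leave that to the full plan, so nothing rests on it here. A group-by-time mixed model accompanied by ANCOVA is also a recognised approach.

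What survives is what the text itself fixes. The mixed models carry the primary label, their pairwise tests are gated, baseline 6MWT is absent from their listed covariates, and the ANCOVA has no stated role. The ANCOVA's presence shows that an efficient test is available; it does not make that test the deciding one.

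**Conclusion.** The point holds in this limited form. The primary outcome has two competing analyses, the one labelled primary is the less efficient for a visit difference, and neither the deciding test nor the deciding visit is fixed. The sample size matches a single contrast and not the gated route.

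The loss depends on how the post hoc pairs are read. Read as raw visit differences, power at T4 stays at about 35–49% at every correlation tried. Read as change from T1, the shortfall against the ungated baseline-adjusted contrast is about 30 percentage points at correlation 0.5, about 15 at 0.7, and small at 0.8.

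These sizes rest on T4 being decisive, equal correlation between visits, 22 to 23 evaluable per group and no age or sex effect. The ambiguity about which result decides rests on none of them. This should be settled before analysis; it does not invalidate the design.

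**What to change.** Make one model primary for 6MWT:

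- Outcomes: 6MWT at T2, T3 and T4.
- Fixed effects: group, visit, group-by-visit, baseline (T1) 6MWT by visit, age and sex.
- Decisive test: the group contrast at one named visit, two-sided 0.05, with no requirement that the interaction be significant first. T4 is the natural choice as the last visit with a 6MWT, but the sponsor must name it.
- Supportive: the other visits and the interaction, estimated from the same model. The separate visit-wise ANCOVAs are then unnecessary, or can be labelled as sensitivity analyses.

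The sample-size paragraph should state that it refers to this contrast.

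The cost is analysis-plan wording; data and software stay the same, and the planned missing-data method need not change. The Data management section defers analysis until all assessments are final, so the wording can be settled first. The price is that the interaction and the non-decisive visits lose confirmatory status.

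### Holm's step-down adjustment could replace single-step Bonferroni in the post hoc tests: same 5% familywise control, never fewer rejections, and a modest power gain if several visits differ

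*Protocol article*

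**What the plan says.** The Statistical analysis section of the protocol article fits a linear mixed model with group, categorical time and their interaction, adjusted for age and sex. It continues that, if the interaction is significant, "Bonferroni-adjusted post hoc tests will be used to identify pairwise differences". It does not say which pairwise differences form the family: the group contrasts at each visit, the visit pairs within each arm, or both. The significance rule is general: "A two-sided p-value < 0.05 will be considered statistically significant for all tests". A separate paragraph adds baseline-adjusted ANCOVA at each time point and mentions no multiplicity adjustment there.

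The Sample size calculation section supplies the design inputs: "Assumptions included a two-sided α = 0.05, statistical power (1 − β) = 0.80", "a clinically relevant between-group difference (Δ) of 60 m" and "a standard deviation (σ) of 80 m". It concludes that "the estimated requirement was 23 participants per group (n = 46 in total") and that "the final target sample size was increased to 28 participants per group, resulting in a total of 56 participants". No power target is set for the post hoc tests. The walk test is measured at T1 to T4, so there are three post-baseline visits; T5 is a telephone interview.

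**The concern.** Bonferroni compares every p-value in a family of m tests with 0.05/m. Holm orders the p-values and compares the smallest with 0.05/m, the next with 0.05/(m−1), and so on, stopping at the first failure. Both hold the familywise error at 5% whatever the dependence between tests. Holm's thresholds are never stricter, so no rejection is lost by using it.

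At stake is some avoidable loss of power in a small trial. The protocol's Conclusion hopes to learn in which phases support is most effective. That depends on which individual visits are declared different, and this is where the two methods can disagree.

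**Working it through.** **The plan's own figure.** The article gives no power figure for the post hoc tests, so there is none to reproduce directly. The only related figure is the sample size. The standard two-sided formula with the stated inputs gives

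n = 2 × (1.960 + 0.842)² × 80² / 60² = 27.9, so 28 per group, not 23.

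That discrepancy is a separate matter. Here it means only that both 23 and 28 evaluable per arm are worth examining.

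**Inputs.**
- From the article: difference 60 m, SD 80 m, 23 or 28 per arm, two-sided 0.05, three post-baseline walk tests.
- Assumed, because the article does not give them: correlation between visits (0.5 and 0.7), the true effect at each visit, and the family (the three visit-wise group contrasts, m = 3).

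**Hand check for one contrast, no baseline adjustment, normal approximation.** SE = 80 × √(2/23) = 23.59 m and 60/23.59 = 2.543.

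| Threshold | Critical z | Power, 23 per arm |
|---|---|---|
| 0.05/3 (Bonferroni; Holm step 1) | 2.394 | 56% |
| 0.05/2 (Holm step 2) | 2.241 | 62% |
| 0.05 (Holm step 3) | 1.960 | 72% |

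Holm reaches the second and third rows only when other contrasts in the family have already been rejected. Its power for a given contrast therefore lies between the first and last rows, and how far it rises depends on how many other contrasts are truly non-null. With 28 per arm (SE 21.38 m) the three powers are 66%, 71% and 80%.

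**Simulation without the interaction gate.** 20,000 trials per row, 23 per arm, contrasts adjusted for T1, family of three. Entries are power for the T4 contrast, Bonferroni to Holm.

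| True effect at T2/T3/T4 (m) | r = 0.5 | r = 0.7 |
|---|---|---|
| 60/60/60 | 66% to 75% | 84% to 91% |
| 0/60/60 | 66% to 70% | 85% to 88% |
| 0/0/60 | 65.7% to 65.8% | 84.0% to 84.1% |

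In the 0/60/60 case the rate of false T2 claims under Holm is about 4%, still under 5%. The chance of at least one rejection is identical under both methods in every row, because the first step is the same test at 0.05/3. Without baseline adjustment, power with 60 m at all three visits goes from 56% to 63–64% (23 per arm) or from 66% to 73–74% (28 per arm), and the gain with two of three is again about 3 points.

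**Simulation with the interaction gate.** 200,000 replicates, contrasts not adjusted for T1, tests counted only when a 3-df group-by-time test is significant, family of three, 23 per arm.

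| Pattern | r = 0.5 | r = 0.7 |
|---|---|---|
| 60 m at all three | 44% to 50% | 53% to 60% |
| 60 m at two of three | 52% to 54% | 55% to 58% |
| 60 m at one of three | no change to one decimal (49.8%) | 54.6% to 54.7% |

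The gains are about 6 to 7, 3 and 0 points. With 28 per arm they are 6.3 to 6.8, about 3 and at most 0.1. If T1 is counted as a fourth contrast, they fall to about 3.5 to 4.6, 2 and 0.

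**Family of one.** If the adjustment is applied separately within each visit, there is a single group contrast, m = 1, and Bonferroni and Holm coincide.

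**The case against.** The strongest reply is that nothing is wrong. Bonferroni is conventional and valid, the tests are a gated follow-up, and the sample size makes no promise about them. All of that stands, and it is why this is a suggestion and not a correction.

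Three further points also stand.
- Bonferroni has simultaneous confidence intervals that match its tests; Holm has no simple equivalent. The article does not promise such intervals for these contrasts, so the loss is small, but it is a real downside.
- The gain rests on assumptions. The family is undefined and the correlations are not in the article. The Discussion warns that two weeks of prehabilitation should not be expected to produce substantial adaptation in every participant, so a 60 m effect already at T2 is the favourable case.
- As written, the adjustment belongs to the mixed-model tests and not to the per-visit ANCOVAs. The ungated, T1-adjusted simulation therefore shows the size of the effect without reproducing the written procedure; the gated simulation is closer to it.

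A reader might infer that Bonferroni costs this trial several points of power at every visit contrast for nothing in return. The documents do not support that. The gain disappears when one visit differs or when each visit is its own family, it never changes the chance of finding something, and Bonferroni does offer matching intervals. Extra power for visit pairs within an arm also has little decision value, since those pairs do not estimate the treatment effect.

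**Conclusion.** The point holds as a cheap improvement. Single-step Bonferroni is valid, but Holm offers the same 5% familywise control under the same assumptions and cannot lose a rejection.

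For a family of three post-baseline walk-test contrasts with 23 per arm, SD 80 m and assumed correlation 0.5 to 0.7, the gain per 60 m contrast is about 3 points when two visits differ and about 6 to 9 when all three do, somewhat less after the interaction gate. It is close to zero when only one visit differs, and nil for the probability of any rejection or when each visit's contrast stands alone. The conclusion that Holm is at least as powerful needs none of these assumptions; only its size does.

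**What to change.** In the Statistical analysis section, replace Bonferroni-adjusted with Holm-adjusted post hoc tests, and state that the procedure is applied to the unadjusted p-values within the family of visit contrasts for each outcome. Report ordinary 95% confidence intervals beside the Holm-adjusted p-values and label them as unadjusted, because such an interval can exclude zero while the adjusted test is not significant.

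The cost is a small edit and a short post-processing step for each outcome, done outside the Bonferroni option: take the unadjusted p-values, order them, and compare them with 0.05/m, 0.05/(m−1) and so on. Simple simultaneous intervals that match the tests are given up. No extra participants or assumptions are needed. The Data management section defers analysis until all assessments are final, so the change can be fixed beforehand.

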### Allocation and blinding

Participants will be randomly assigned in a 1:1 ratio to either the IG or CG using computer-generated block randomization (www.randomizer.org), stratified by age and sex. Allocation will be concealed using sequentially numbered, opaque, sealed envelopes handled by an independent researcher not involved in the intervention or outcome assessment.

All participants will be assigned a unique identification code to ensure confidentiality. The outcome assessor will be blinded to the group allocation, and the researcher conducting the intervention will not be involved in any assessment procedures, preserving single-blind conditions.

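### The per-visit ANCOVAs are stated with the T1 value as covariate but without age and sex, the randomisation strata that the primary mixed models adjust for; this costs a little precision where those factors predict an outcome beyond T1

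*Protocol article*

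**What the plan says.** All places are in the Protocol article, Methods.

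- **Allocation and blinding:** participants are assigned 1:1 by "computer-generated block randomization (www.randomizer.org), stratified by age and sex". Block size and age bands are not given.
- **Statistical analysis, mixed-model paragraph:** the primary models contain group, categorical time, their interaction and a participant random intercept. It adds: "Prespecified adjustment variables beyond the main fixed effects will include the stratification factors used in randomization, namely age and sex".
- **Statistical analysis, next paragraph:** "Between-group comparisons at each time point will be conducted using analysis of covariance (ANCOVA), adjusting for baseline values (T1". No other covariate is named for this analysis.

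The mixed model's Bonferroni-adjusted pairwise tests are run only after a significant interaction. The ANCOVAs carry no such condition.

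**The concern.** An analysis should reflect the restrictions imposed by the randomisation. Blocking within age and sex strata makes the arms nearly equal on both factors, so these factors contribute little to the real sampling error of the treatment difference. An ANCOVA on T1 alone does not use this. Whatever age and sex explain beyond T1 stays in its residual variance, and the reported standard error describes a less balanced trial than the one that was run.

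The ANCOVAs supply the treatment difference at each visit whether or not the interaction is significant, for the six-minute walk distance among other outcomes. With 46 to 56 people analysed, precision already gained through stratification is worth keeping. The plan also gives two analyses of the same outcome different covariate sets and states no reason.

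**Working it through.** **Plan's own figures.** The Sample size calculation section states: "Assumptions included a two-sided α = 0.05, statistical power (1 − β) = 0.80", "a clinically relevant between-group difference (Δ) of 60 m" and "a standard deviation (σ) of 80 m". From these it reports that "the estimated requirement was 23 participants per group (n = 46 in total". The usual formula gives

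n per group = 2 × [80 × (1.960 + 0.842) / 60]² = 27.9, rounded up to 28.

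The stated 23 is therefore not reproduced. That is a separate matter and does not affect the point made here. Below, 60 m, 80 m and 23 per group serve only as inputs.

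**Assumed inputs, because the article gives none:** T1-to-visit correlation ρ of 0.5 to 0.7; two age bands by two sexes; blocks of 4; and R², the share of the variance left after T1 that age and sex explain, of 5% to 10%.

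**Step 1: idealised size, with perfect balance.** The reported standard error exceeds the true one by the factor 1/√(1 − R²). The actual two-sided type I error is 2 × [1 − Φ(1.96/√(1 − R²))].

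| R² | SE ratio | Type I error |
|---|---|---|
| 0.05 | 1.026 | 4.4% |
| 0.10 | 1.054 | 3.9% |

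**Step 2: simulation with real blocks.** N = 56, SD 80 m, ρ = 0.7, 6,000 runs under the null, Monte Carlo error about 0.3 percentage points.

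| R² | Dropout | Mean reported SE, T1 only | True SE, T1 only | Ratio | Type I, T1 only | Type I, T1 + age + sex |
|---|---|---|---|---|---|---|
| 0.05 | 0% | 15.35 m | 15.23 m | 1.01 | 4.6% | 5.1% |
| 0.05 | 20% | 17.25 m | 17.02 m | 1.01 | 4.7% | 5.0% |
| 0.10 | 0% | 15.33 m | 14.64 m | 1.05 | 3.7% | 5.1% |
| 0.10 | 20% | 17.28 m | 16.70 m | 1.03 | 4.0% | 4.9% |

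A second simulation over ρ of 0.5 and 0.7, with 56 analysed, gave SE excesses of 1–2% at R² = 0.05 and 5–6% at R² = 0.10. Its type I errors were 4.5–4.7% and 3.7%. Together the two give the range of 1–6% for the SE and 3.7–4.7% for type I error.

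**Step 3: power at 60 m, 23 per group, ρ = 0.5.** The SD after T1 is 80 × √(1 − 0.25) = 69.28 m. The reported SE without age and sex is 69.28 × √(2/23) = 20.43 m. The true SE is 20.43 × √(1 − R²). The t quantiles are 2.017 (43 df) without the two factors and 2.020 (41 df) with them.

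- R² = 0.05, true SE 19.91 m. T1 only: Φ[(60 − 2.017 × 20.43)/19.91] = Φ(0.944) = 82.7%. With age and sex: Φ[60/19.91 − 2.020] = Φ(0.994) = 84.0%. Gain 1.3 points.
- R² = 0.10, true SE 19.38 m. T1 only: Φ(0.970) = 83.4%. With age and sex: Φ(1.076) = 85.9%. Gain 2.5 points.

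**Step 4: when T1 carries the whole effect.** In a simulation where age and sex explain 30% of T1 variance and nothing beyond T1, the T1-only ANCOVA has type I error 5.3%, reported SE 15.3 m and true SE 15.5 m. There is no inflation. In the Step 3 calculation with R² = 0, power is 82.1% without the two factors and 82.0% with them, so adding them costs almost nothing.

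**The case against.** The strongest defence is that the models the article calls primary already adjust for age and sex, so only supporting contrasts are affected. That stands, and it limits the weight of the point. It is also fair to say that the ANCOVA sentence does not exclude further covariates and that a condensed article may leave a full list to an analysis plan. Still, the article does list covariates for each analysis, and the lists differ. Placing age and sex beyond the main fixed effects ties them to the mixed models. If they were meant to apply throughout, the same one-sentence edit says so.

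Three stronger readings are tempting and are not supported:

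- **That the ANCOVAs are conservative wherever age or sex predicts the outcome.** Step 4 shows otherwise. T1 may already carry much of the age and sex effect on measures such as walking distance, and only what remains beyond T1 matters. Larger losses need a larger remainder: at 20%, type I error falls to about 3.0–3.4%. Nothing in the article supports a remainder of that size.
- **That the same fault affects categorical outcomes,** for which the plan says: "Differences in categorical outcomes will be analyzed using the Chi-square test or Fisher’s exact test, as appropriate". No interval is specified for these tests. In simulation Chi-square stayed at 4.9–5.2% with no or modest differences in risk between strata, and fell to 4.0% and 2.9% only when the extreme-stratum risks were 0.6 against 0.2 and 0.8 against 0.2. Fisher's test was already at 3.2% with no stratum effect at all. A stratified or logistic replacement would bring sparse strata or a different estimand. The point does not extend to these tests.
- **That adding age and sex would make the ANCOVA and mixed-model results agree.** The mixed model as described uses all visits and lists no T1 covariate, so the two can differ even with identical age and sex terms.

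**Conclusion.** The point holds as a modest mismatch between the randomisation and the stated per-visit ANCOVAs. The direction is certain: omitting stratification factors that predict the outcome beyond T1 makes the standard error too large and the test conservative. It produces neither bias nor an excess of false positives. The size depends on assumptions about block size, age bands, the T1 correlation and the residual share explained by age and sex. At a residual share of 5–10%, the figures are an SE about 1–6% too large, type I error of about 3.7–4.7%, and about 1–2.5 power points at 60 m. At a share of zero there is no loss. The primary mixed models are unaffected.

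**What to change.** In the Statistical analysis section, replace the ANCOVA sentence with:

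> Between-group comparisons at each time point will use ANCOVA adjusting for the baseline value (T1) and the randomisation stratification factors, age and sex.

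The cost is one sentence and about two degrees of freedom (more if age is entered as more than two bands). Both variables are already recorded for randomisation, and no further patients or data are needed. The Data management section defers analysis until recruitment and all assessments are complete, so the change can be specified before any analysis. The sentence on Chi-square and Fisher tests need not change on this account.
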